## The System

A generic database management system (DBMS) based on EpiData has been designed by CRO. The system includes data entry, editing, reporting of errors and status of work, data documentation, security, and confidentiality of the data. Appropriate use of the system will ensure valid data are stored, complete and accurate, and that the necessary information is available for data analysis. The management control of the DBMS proposes the data are properly archived and stored at TigerMed (CRO), and enough precautionary measures are taken from accidental damage or loss of data. The design and management of the DBMS also promises confidentiality and non-violation of the human participation protection right.

## Data checking and coding

CRFs will be completed for each enrolled patient by investigators. After checking by clinical monitor, the original copy will be sent to data manager for data entry and data management. The in-house variables coding will be processed by data manager at TigerMed.

## Data checking, data entry and error checking

Batch processing system, which will benefit internal management of the data, such as data entry, error checking, updating, and reporting, has been chosen for the data entry get a sequential number. The data will be entered twice, and the key punching errors are to be detected by a module included in the system. The data errors are classified as incompleteness of the forms, duplications, range errors, inconsistencies, and link problems. Al these checks are included in a module within the system. Invoking the module will yield the list of all those kinds of problems in the data. These lists are to be used to resolve the problem and are to be kept properly as future reference. The detailed documentation of the check plans goes along with the system. The data errors will be reviewed and revised by investigator and clinical monitor before any modification with data entry system.

## Data freezing

Dataset will be modified in terms of the revisions targeted to error list from investigator. Any dataset modification and updating will be well documented for potential SFDA inspection in the future. After modification, the dataset will be frozen and transported to biostatistician for analysis.

# Statistical Methods

All data will be double entered into custom-made data entry programs. The data management programs include range and consistency checks. An SAS program (SAS Institute Inc., Cary, NC, USA ) will be applied for statistical analysis.

- 1. Safety

The safety analysis will be performed based on the safety set (SS). It will include patients who received at least one injection, and completed at least one interview of safety evaluation after injection.

Three-wise comparison employed the chi square test, or Fisher’s exact test when data were sparse, for dichotomous outcomes will be performed to test the difference of occurrence of adverse events among placebo, 30 μg YIC and 60 μg YIC groups. A p-value < 0.05 (two-tailed) will be considered statistically significant.

- 1. Efficacy

The efficacy analysis will be conducted based on both full analysis and per-protocol sets. For full analysis set (FAS), it will include patients who were randomized, received at least one injection, and completed at least one interview of efficacy evaluation after injection. The intent-to-treat principle will be applied for the dataset. For per protocol set (PPS), it will include patients who met following three conditions：

1. Baseline information are available；
2. Complete full course of treatment and follow-up without protocol violation；
3. With good compliance (between 80% and 120%）.

For those important indicators, the missing data will be estimated using the most previous observation (LOCF, last observation carry forwards).

The primary efficacy hypotheses will be tested for response rate of primary endpoint in 30 μg YIC or/and 60 μg YIC groups > that in placebo group (2-tailed). The Chi square test, or Fisher’s exact test when data were sparse, will be employed. A p-value, point estimate, as well as confidence interval will be calculated.

The secondary efficacy outcomes will be summarized in a similar fashion.

Repeated measures analysis will be performed using a generalized estimating equations (GEEs) method to adjust the dependence among repeated observations made on the same patient while testing the group and time effects. A p-value < 0.05 (two-tailed) will be considered statistically significant.

- 1. Sample size

The sample size was calculated to ensure an adequate evaluation of the primary endpoint. Based on the literatures and the results of phase IIa trial, a sample size of 78 patients per arm could detect a difference of primary response rate between 60 µg group, 30 µg group and placebo group (response rate in 60 µg YIC group vs placebo group, 35% vs 3%; and response rate in 30 µg YIC group vs placebo group, 20% vs 3%) with a statistical power of 80% at the 0.05 level of significance, allowing for a dropout rate of 20%.

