# Rationale

- 1. General Introduction

Viral hepatitis B is highly endemic in China, with estimated 130 million chronic hepatitis B surface antigen carriers. Of these, 30 million infected individuals are chronic active hepatitis patients who need antiviral therapy, which mostly relies on interferon  and lamivudine. The short-term efficacy response to interferon  is 40-60%, which reduces to 20-40% one year after the treatment, and its use is associated with dose-related side effects. For lamivudine, after one year consecutive treatment, the loss of HBeAg reaches 20-25%, and HBeAg seroconversion rate is 15-20%. However, the use of lamivudine for more than 6 months is associated with the emergence of resistant YMDD variants. Furthermore, rebounds of HBV DNA are frequently observed after longer period of treatment. Hence, effective immuno-modulating drugs or products to enhance host immune responses aiming to break immune tolerance to hepatitis B virus (HBV) is encouraged.

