### Discontinuation/Withdrawal

Any patient who had signed a consent form, and meet the following criteria will be defined as premature withdrawal.

1. Patients who request to quit themselves;
2. Patients who violate the study protocol;
3. Patients who become pregnancy;
4. Patients who are unblinded due to SAE;
5. Patientsduring the treatment period who developed the following symptoms
   - - - Hepatic cirrhosis
       - Hepatic failure
       - And hepatoma.

If the withdrawal occurs due to the adverse events or abnormal laboratory tests, details should be recorded in the CRFs.

- 1. Laboratory assay

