### Treatment and follow-up of adverse events

Any adverse event must be treated with acceptable method. Investigators must report and discuss with SPONSOR when a method repelling with study agent has to be implemented, since this activity will cause premature withdrawal. All adverse events should be followed-up until the event has: resolved or subsided or stabilized or disappeared or the event is otherwise explained.

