### Primary endpoint

The primary endpoint was defined as loss of HBeAg, or presence of anti-HBe antibody or suppression of HBV DNA.

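### LOCF without exception by reason for missingness can count an early virologic response as a week-44 response in a patient who was withdrawn, and the FAS rule sits badly with the stated intent-to-treat principle

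*Protocol*

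**What the plan says.** **Missing data.** Protocol 6.2 Efficacy has one rule, for indicators it calls important but does not list: "the missing data will be estimated using the most previous observation (LOCF, last observation carry forwards"). The reason for missingness plays no part.

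**Analysis set.** The full analysis set (FAS) holds patients "who were randomized, received at least one injection, and completed at least one interview of efficacy evaluation after injection". The next sentence reads "The intent-to-treat principle will be applied for the dataset".

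**Endpoint.** 4.6.2: "The primary endpoint was defined as loss of HBeAg, or presence of anti-HBe antibody or suppression of HBV DNA". Any one component makes a responder. Section 4.6.1 names two assessment times, weeks 24 and 44, without saying which is primary.

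**Sampling.** After baseline, serum for virology is taken at weeks 12, 24, 36 and 44 only (4.3.4 to 4.3.6; Appendix 2).

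**Ways out of the trial.**
- 4.3.8 lists withdrawal for protocol violation and, during treatment, for cirrhosis, hepatoma or "Hepatic failure".
- 4.8 prohibits antiviral and immunomodulating therapy, so its use can be a violation.
- 4.5.7 says of treatment incompatible with the study agent that it must be discussed with the sponsor, "since this activity will cause premature withdrawal".
- 4.3.7 classes an unblinded patient as lost to follow-up.

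None of these sections says that such a patient counts as a non-responder.

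**The concern.** Week 44 is there to show whether a response lasts once injections stop. LOCF answers that question by assumption: a response seen once is taken as permanent. The Protocol's own background argues against this. For interferon it gives a short-term response of 40–60%, "which reduces to 20-40% one year after the treatment", and for lamivudine it reports frequent HBV DNA rebound with longer treatment (2.1).

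A patient with a fall in HBV DNA at week 12 who then stops because of liver deterioration, or who starts a prohibited antiviral, would be carried 32 weeks (44 − 12) as a success. If such patients are commoner in the vaccine arms, the comparison with placebo is distorted as well as the rates.

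The FAS rule adds a second problem. Efficacy rests on HBV DNA, HBeAg and HBeAb (4.6), first measured after baseline at week 12. If that sample is the first efficacy evaluation, randomised and injected patients who leave earlier are removed, which is not intent-to-treat.

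**Working it through.** **Plan's own figure.** Section 6.3 gives 78 per arm for 80% power at 0.05, with 20% dropout. The limiting comparison is 20% vs 3%. Exact two-sided Fisher with 62 evaluable per arm gives 81.9% power, and 62 / (1 − 0.20) = 77.5, so 78. The figure reproduces and is not in dispute.

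**Inputs.** 80 per arm (synopsis); 20% dropout, so 80 × 0.20 = 16 per arm; response 35%, 20% and 3% (6.3). The share of early responses later lost is an assumption borrowed from the interferon figures: 1 − 40/60 = 1/3 to 1 − 20/40 = 1/2.

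**Responses credited by LOCF that would have been lost**, if every dropout has a post-baseline sample and responds at the planned rate (16 × rate × share lost):

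| Arm | Patients of 80 | Percentage points |
|---|---|---|
| 60 µg | 16 × 0.35 × (1/3 to 1/2) = 1.9 to 2.8 | 2.3 to 3.5 |
| 30 µg | 16 × 0.20 × (1/3 to 1/2) = 1.1 to 1.6 | 1.3 to 2.0 |
| Placebo | 16 × 0.03 × (1/3 to 1/2) = 0.16 to 0.24 | 0.2 to 0.3 |

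These are upper-end figures. Patients who leave before week 12 have no post-baseline value to carry.

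**LOCF against non-responder imputation.** Let q be the share of dropouts whose last observation is a response (not given in the Protocol). LOCF exceeds non-responder imputation by 0.20 × q: 2, 6 and 10 points for q = 10%, 30% and 50%.

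**Effect on the test.** Suppose the true sustained rate is 3% in both arms, with 80 per arm. The analysed rate is 0.80 × 0.03 + 0.20 × q. Exact rejection rates at two-sided 0.05:

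| q vaccine / placebo | Chi-square | Fisher |
|---|---|---|
| 3% / 3% | 4.3% | 0.7% |
| 20% / 10% | 7.2% | 3.6% |
| 20% / 3% | 14.8% | 7.7% |
| 30% / 3% | 28.5% | 18.9% |

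The test is inflated only when q differs between arms. With equal q it stays near or below its nominal level, although both rates remain higher than under non-responder imputation.

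**The case against.** **Direction.** A reader might infer that LOCF necessarily favours the vaccine. The documents do not support that. LOCF carries non-response too, and section 2.1 says that responses to immunotherapy should be looked for some time after the last injection. A vaccine patient who leaves early may carry a non-response that would have become a response. This stands.

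**Size.** The fade rate concerns another drug, one year after treatment. LOCF here spans at most 32 weeks, or 20 from week 24. This stands; the table is an illustration, not an estimate.

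**Significance.** It is tempting to say that one carried responder decides the trial. By Fisher, with 2/80 on placebo, 10/80 gives p = 0.032 and 9/80 gives p = 0.056. But the plan uses chi-square unless data are sparse. At 9 vs 2 the smallest expected count is (9 + 2)/2 = 5.5, above the usual cut-off of 5 (an assumption, since the plan gives none), and chi-square gives 0.029. Its boundary lies between 9 (0.029) and 8 (0.050). Every discrete test has such a boundary. At the planned rates (16/80 vs 2/80) p is below 0.001, and with two vaccine responders removed (14/80 vs 2/80) it is still below 0.003 by either test.

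**Who is affected.** Rescue therapy is not a term in the Protocol; only incompatible treatment and prohibited medication are described. Hepatic failure is a withdrawal reason only during treatment, and it is not part of the virologic endpoint. Nothing says that sampling stops after withdrawal; if it continues, fewer values are missing.

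**FAS.** The efficacy interview is undefined, and the synopsis uses the word interview for every visit. Read that way, few patients are excluded, and those without later virology would carry baseline non-response.

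**Safeguards.** The per-protocol analysis leaves out withdrawn patients, a GEE analysis is planned, and carry-forward to week 24 spans at most 12 weeks. These are partial safeguards: the rule for the FAS is unchanged.

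**Conclusion.** The concern holds as a defect in the missing-data rule. As written, LOCF can credit a withdrawn or unblinded patient with a week-44 response that nobody observed. Relative to counting such patients as non-responders, it raises the sustained response rate by 0.20 × q at the planned dropout.

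As an upper-end illustration, up to about 2–3 of 80 responders at 60 µg, 1–2 at 30 µg and 0.2 on placebo would be credited wrongly. This rests on the planned rates and dropout, a post-baseline sample in every dropout, and a borrowed fade of one third to one half.

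The comparison is biased towards the vaccine only if transient responses are commoner among vaccine dropouts. The planned 35% and 20% against 3% make that plausible, not certain. The FAS definition conflicts with the intent-to-treat statement if the efficacy evaluation means the week-12 sample; otherwise it is an ambiguity to settle.

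This is a point that should be fixed. A stronger grade would need a certain direction or a demonstrated reversal of the result, and the documents give neither.

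**What to change.** In 6.2, for the week-44 analysis of the primary endpoint:
- include all randomised patients in their assigned arm;
- count a missing week-44 result as non-response;
- count a response recorded after the start of prohibited antiviral or immunomodulating therapy as non-response;
- keep LOCF, the per-protocol set and a GEE on observed data as sensitivity analyses.

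**Cost.** Wording only, with no extra patients under the planned assumptions. If week-44 completers respond at the planned rates, imputation gives 0.80 × 20% = 16% at 30 µg and 0.80 × 3% = 2.4% on placebo. Exact power at 80 per arm is then 83% (Fisher) to 88% (chi-square, with Fisher when an expected count is below 5). For 60 µg (28% vs 2.4%) it exceeds 99%.

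That reassurance depends on the planned rates being week-44 rates. If responses fade by one third to one half in both arms, the 30 µg comparison becomes about 10.7% vs 1.6% down to 8% vs 1.2%. Power is then about 57% down to 37% (Fisher), or 61% down to 39% (combined rule).

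**Downside.** Non-responder imputation understates the response rate if dropout is unrelated to outcome. In the same illustration it would miss 16 × 0.20 × (1/2 to 2/3) = 1.6 to 2.1 sustained responders at 30 µg. It is the cautious choice rather than an unbiased one, which is why LOCF should stay as a sensitivity analysis.

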### Definition of endpoints

The virologic response will be assessed four weeks after the end of treatment (week 24) and at the end of follow-up (week 44). HBeAg seroconversion was defined by the loss of HBeAg and the presence of anti-HBe antibody. Suppression of HBV DNA was defined as > 2 log10 decrease of viral load.

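### Either dose can carry the primary claim at an unadjusted 0.05, and neither a deciding visit nor a deciding analysis set is named

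*Protocol*

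**What the plan says.** - **Hypothesis.** Section 6.2 (Efficacy) states "The primary efficacy hypotheses will be tested for response rate of primary endpoint in" the 30 µg *or/and* 60 µg groups. The sentence goes on "groups > that in placebo group (2-tailed", so it is written in one direction but tested two-sided.
- **Test.** "The Chi square test, or Fisher’s exact test when data were sparse, will be employed".
- **Timing.** Section 4.6.1: "The virologic response will be assessed four weeks after the end of treatment (week 24) and at the end of follow-up (week 44". Section 4.6.2 defines the endpoint itself with no visit: "The primary endpoint was defined as loss of HBeAg, or presence of anti-HBe antibody or suppression of HBV DNA". The synopsis repeats both statements and ranks neither visit.
- **Analysis sets.** "The efficacy analysis will be conducted based on both full analysis and per-protocol sets", with no statement of which one leads. A GEE analysis with its own two-tailed 0.05 threshold follows.
- **Level.** Section 6.3 sizes both dose comparisons "with a statistical power of 80% at the 0.05 level of significance, allowing for a dropout rate of 20" per cent. No alpha split, testing order or gate appears anywhere in the protocol.

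**The concern.** The *or/and* wording lets success on one dose stand as success of the primary hypothesis. Two comparisons against a shared placebo arm, each at 0.05, do not have a joint error of 0.05. If the endpoint is also tested at each of the two visits, there are four such comparisons.

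This goes beyond detail that a protocol may leave to a statistical analysis plan. The protocol itself fixes the either-dose hypothesis, the 0.05 level and an endpoint tied to two unranked visits. A later plan that added control would be changing the primary claim set here.

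Two things are at stake: the chance of carrying an ineffective vaccine forward, and the reading of mixed results. If 30 µg were positive at week 24 only, or in the PPS only, the protocol would give no rule for whether the trial succeeded.

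**Working it through.** **Inputs from the protocol.** 80 per arm, allocated 1:1:1. Sample size stated as 78 per arm, 80% power, 0.05, 20% dropout. Planned response: "YIC group vs placebo group, 35% vs 3" per cent for 60 µg, and 20% against 3% for 30 µg. Evaluable patients after dropout: 78 × 0.8 = 62.4, taken as 62; 80 × 0.8 = 64.

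**Inputs assumed.** The week 24/44 correlation is not given, so 0.4–0.8 is used. Common response rates of 3% to 25% are used under no effect. Fisher's test is taken to replace chi-square when an expected count is below 5.

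**1. The protocol's own figure.** The 30 µg comparison binds. The unpooled formula is

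n = (z₁₋α/₂ + z₀.₈)² × [p₁(1−p₁) + p₂(1−p₂)] / (p₁−p₂)²,

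with 0.20 × 0.80 + 0.03 × 0.97 = 0.1891 and 0.17² = 0.0289.
- At 0.05: n = 51.4, and 51.4/0.8 gives 65.
- At 0.025: n = 62.19, and 62.19/0.8 = 77.7 gives 78.
- Other methods at 0.05: pooled 55, giving 69; Fisher exact 60, giving 75; continuity-corrected 66, giving 83 by division by 0.8 or 80 by multiplication by 1.2.

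So 78 matches exactly with a two-way split of alpha and comes within two of a common calculation at 0.05. The number does not settle which was meant. The text says 0.05.

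**2. Bounds.** For independent tests, the chance of at least one false positive is 1 − 0.95² = 9.75% for two tests and 1 − 0.95⁴ = 18.5% for four. With a shared placebo arm the two dose statistics correlate at 0.5, and by normal theory the two-dose figure is 9.1%. For four tests it is 16.1%, 14.9% and 12.6% at between-visit correlations of 0.5, 0.7 and 0.9.

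**3. Simulation of the chi-square/Fisher rule under no effect** (80 per arm, two-sided 0.05 per test, between-visit correlation 0.4–0.8):

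| Common response rate | Two doses, one visit | Two doses, both visits |
|---|---|---|
| 3% | about 1.4% | 2.3–2.8% |
| 5% | below 5% | about 6.5–7.5% |
| 8.3% | about 8% | 12.5–14.8% |
| 20% | about 9% | 13.9–16.7% |
| 25% | about 9% | 14.3–17.1% |

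From 8.3% upward, false claims of benefit (wrong rejections in favour of the vaccine) run at about 4–5% for two doses at one visit and about 6–9% for both visits. A single two-sided test at 0.05 would give 2.5% in that direction. Any further inflation from choosing among FAS, PPS and GEE is not counted.

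**4. Power with Hochberg at one visit** (62 evaluable per arm, Fisher, placebo 3%, 30 µg 20%):
- 60 µg at 35%: 30 µg power is 82% with or without adjustment; 60 µg power moves from 99.8% to 99.7%.
- 60 µg inactive at 3%: 30 µg must in effect reach 0.025, and its power is about 74%.

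Simulated familywise error with Hochberg at 80 per arm stays within 5% at rates from 8.3% to 25%.

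**The case against.** **At the planned placebo rate the error is below 5%.** This stands. A reader might infer that the trial simply fails to hold its 5% level. The document does not support that: at a common 3% response, even four tests give only 2.3–2.8%. But this protection comes from sparse data and goes as response rises. With both visits tested it is gone by about 5%. The endpoint counts any one of three components, and section 2.1 reports one placebo patient with HBV DNA suppression in phase IIa. That is about 1/12 = 8.3% if the 36 patients were split equally, which is not stated, and under a different definition of suppression. So 8.3% is an illustration, not an estimate, and rates of 20–25% have no source in the protocol.

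**Testing at both visits is not stated.** Also correct. The protocol says the response is assessed at weeks 24 and 44; no sentence makes each visit a separate primary test, or says that a positive result in any visit, analysis set or GEE model would suffice. The 12–17% range is therefore conditional. The 8–10% range needs only the either-dose hypothesis.

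**The benchmark of 2.5% is not in the protocol.** True. It follows from a single two-sided 0.05 test, and against a nominal 5% the two-dose false-benefit rate of 4–5% looks acceptable. Both measures are therefore given.

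**The analysis plan may add control, and 78 hints at a split.** Running both FAS and PPS, or adding a GEE, is not an error in itself. The exact match at 0.025 is suggestive, but if a split was intended, section 6.3 misstates the level.

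**This is a phase IIb dose-finding trial.** Strict familywise control matters less here than in a confirmatory trial. Even so, the protocol sets out a formal powered test and uses it to work out the optimal dosage, so the rule for reading it should be fixed.

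**Conclusion.** The point holds, with limits. The protocol sets an either-dose primary hypothesis at 0.05 with no multiplicity control, and leaves open which visit and which analysis set decide.

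- Firm part: at a common response of about 8% or more, two doses at one visit give a two-sided familywise error of about 8–10%, and about 4–5% for false benefit.
- Conditional part: if both visits are tested, about 12–17% and about 6–9%, assuming a between-visit correlation of 0.4–0.8.
- Not supported: that the error exceeds 5% under the planned 3% response.

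The lack of an agreed reading for conflicting visits or analysis sets is a defect at any response rate.

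**What to change.** Amend sections 4.6 and 6.2 before unblinding:
1. Name one visit in the FAS as the single primary analysis, for example week 44 as the end of follow-up. Section 2.1 gives reasons for both visits and ranks neither, so the essential step is to name one.
2. Make the other visit, the PPS and the GEE supportive.
3. Test the two doses against placebo with Hochberg: claim both if both p ≤ 0.05; otherwise claim only the one with the smaller p-value, and only if it is ≤ 0.025.
4. State in section 6.3 which alpha and formula produced 78.

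**Cost.** A result at the other visit alone can no longer carry the claim. At the planned rates no patients are added. The 82% power for 30 µg depends on 60 µg working; if 60 µg is inactive, it is about 74% with 62 evaluable per arm. Section 2.2 leaves open that 30 µg may be the optimal dosage, so the protocol should state this figure. To reach 80% in that case with Fisher at 0.025, about 72 evaluable per arm are needed (power 81%; 70 give 79.5%), or 72/0.8 = 90 enrolled per arm. A fixed order of the two doses would also hold 5% without more patients, but the second dose could not be claimed if the first failed.

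### The primary efficacy test is fixed without adjustment for baseline HBV DNA and ALT, leaving a cheap and mostly modest gain in power and precision unused

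*Protocol*

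**What the plan says.** Protocol section 6.2 (Efficacy) names the primary test: "The Chi square test, or Fisher’s exact test when data were sparse, will be employed". It is two-sided, and no covariate or stratification factor is attached to it. The only model-based efficacy analysis is a GEE, used "to adjust the dependence among repeated observations made on the same patient while testing the group and time effects"; no baseline term is named there either.

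The primary endpoint (section 4.6.2) is binary and is met by any one of three components. One of these is defined against baseline (section 4.6.1): "Suppression of HBV DNA was defined as > 2 log10 decrease of viral load".

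HBV DNA above a threshold and ALT between 2 and 10 times the cutoff are entry criteria (section 4.2.1). Both are therefore measured in every enrolled patient at screening (section 4.3.2), and section 4.4.2 takes the screening results as baseline. Section 7 randomises within centre in blocks of six, with no stratification by viral load or ALT.

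**The concern.** Two baseline measurements exist for every patient. One of them is built into the outcome, and neither the design nor the primary analysis uses either for balance or precision. If they predict response, an unadjusted test gives up some power, and the reported risk difference carries any chance difference in baseline between arms. Adding them costs no patients and no data.

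The protocol's own figures show why baseline load matters to the outcome. The assay detection limit is 500 copies/mL (section 4.4.1), which is log10(500) = 2.70. I read the entry threshold as 1×10^5 copies/mL, since its symbols are lost in the text. A patient entering there can show a fall of at most 5 − 2.70 = 2.30 log10, and must drop below 1,000 copies/mL to count. A patient entering at 10^8 need only drop below 10^6. Defining response as a change from baseline does not remove dependence on baseline. It can build it in.

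**Working it through.** **Inputs from the protocol (section 6.3).** "a sample size of 78 patients per arm could detect a difference of primary response rate"; for 30 µg, "YIC group vs placebo group, 20% vs 3" (per cent); for 60 µg, "YIC group vs placebo group, 35% vs 3" (per cent); "with a statistical power of 80% at the 0.05 level of significance, allowing for a dropout rate of 20" (per cent). The 30 µg comparison has the smaller difference and so drives the sample size.

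**The plan's own figure.** 78 × (1 − 0.20) = 62.4, so about 62 evaluable per arm. Exact Fisher power, two-sided 0.05, 20% against 3%, at 62 per arm is 81.9%. In reverse, 62/0.8 = 77.5, which rounds up to 78. (The smallest n reaching 80% is 60, and 60/0.8 = 75.) The stated size is therefore consistent with an unadjusted Fisher test, and the 80% target is met. The uncorrected chi-square has 85.2% by normal approximation and about 89% to 90% by simulation. For 35% against 3%, power is above 99%.

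**Assumption.** The documents do not say how strongly baseline HBV DNA or ALT predicts response. I represent them by one standardised baseline score with a log-odds slope of 0 to 1.5 per SD, which corresponds to an AUC of 0.50 to 0.82.

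**Method.** Logistic outcome with the marginal response rates held fixed, 62 per arm, 4,000 runs per setting. The Pearson chi-square is compared with a logistic score test adjusted for the baseline score.

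| Rates | AUC | Unadjusted | Adjusted | Gain (points) |
| --- | --- | --- | --- | --- |
| 20% vs 3% | 0.50 | 89.6% | 89.4% | −0.2 |
| 20% vs 3% | 0.63 | 89.6% | 89.8% | 0.2 |
| 20% vs 3% | 0.70 | 89.4% | 90.1% | 0.7 |
| 20% vs 3% | 0.74 | 89.5% | 91.6% | 2.1 |
| 20% vs 3% | 0.82 | 90.3% | 94.8% | 4.5 |
| 25% vs 10% (assumed) | 0.50 | 59.4% | 60.5% | 1.1 |
| 25% vs 10% (assumed) | 0.64 | 60.9% | 63.2% | 2.3 |
| 25% vs 10% (assumed) | 0.74 | 59.6% | 65.6% | 6.0 |
| 25% vs 10% (assumed) | 0.82 | 59.5% | 71.6% | 12.1 |

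With 4,000 runs, the standard error of a power near 60% is √(0.6 × 0.4/4000) = 0.8 points. A repeat of the last row gave a gain of about 13 points, so I quote 1 to 13.

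A Firth penalised likelihood-ratio test at 20% vs 3% agrees: 90% to 92%, 89% to 93% and 90% to 96% at slopes of 1, 1.5 and 2 per SD. Slope 2 is very strong: an odds ratio of 7.4 per SD and an AUC of 0.87. At 25% vs 10% it gives 60% to 77%, and I do not rely on it there. For 35% vs 3% there is nothing to gain.

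**Type I error at a common 10% rate.** Unadjusted 4.7% to 5.4%; adjusted score test 4.9% to 5.6%; Firth 4.7% to 5.7%. At a common 3% rate the Firth test is conservative, at 2.1% to 2.6%.

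**Chance imbalance.** The standard error of a difference in baseline means is √(2/62) = 0.180 SD, so the 95% range reaches 1.96 × 0.180 = 0.35 SD. At 20% vs 3% an imbalance of that size moves the observed risk difference by about 2 to 4 points (slopes 0.8 to 1.5). An unadjusted estimate leaves this in.

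**Events available to a model.** 62 × 0.20 = 12.4 and 62 × 0.03 = 1.9, so about 14 responders in the 30 µg comparison, about 2 of them on placebo.

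**The case against.** The opposing case is substantial, and most of it limits the size of the point.

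- *The test is valid.* Randomisation protects the type I error, as the figures above show. A reader might infer that the unadjusted difference is biased. It is not: over repeated randomisation it is unbiased, and chance imbalance is already reflected in its standard error. What adjustment corrects is the estimate given the imbalance that actually occurred.
- *Planned power is met.* A reader might infer that the trial is underpowered without adjustment, or that a correlation of 0.5 lifts power from 80% to Φ((0.84 + 1.96)/√0.75 − 1.96) = 90%. The protocol supports neither. Its size already delivers 81.9% by Fisher. The variance rule belongs to linear models, and the simulated chi-square starts at 89% to 90%, not 80%.
- *Prognostic strength comes from outside the documents.* This stands, so only ranges can be given. The 10% placebo rate is also an assumption. The phase IIa summary (section 2.1) reports one placebo patient with suppression among 36 patients in three groups. With equal arms, again an assumption, that is 1/12 = 8.3%, on one component and by a different cut-off.
- *The full analysis set is larger than the completers.* With LOCF it may approach the 80 enrolled per arm, where the gain at 20% vs 3% is 0 to 3 points.
- *Adjusted models struggle with about 2 placebo events.* In a simulation with two covariates, Firth fits put a true 3% placebo risk at 3.7% to 3.9%. At slope 1, the SD of the risk difference fell only from 0.055 to 0.052, a variance ratio of (0.052/0.055)² = 0.89. This restricts the method and the number of covariates; it does not rule adjustment out.
- *An unseen SAP may add adjusted analyses.* It may; Appendix 1 lists CMH and ANOVA, which section 6 does not use. But section 6.2 positively names the unadjusted test for the primary hypothesis.
- *Baseline DNA is not wholly ignored.* True, because one of three alternative components is a change from baseline. That is not adjustment for baseline.

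**Conclusion.** The point holds as one of efficiency and precision. The protocol commits its primary comparison to an unadjusted test and its GEE to group and time, while two baseline measurements available on every patient are neither balanced by design nor used.

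At the protocol's own 20% vs 3% with 62 evaluable per arm, the gain is about 0 to 2 points of power for weak to moderate covariates (AUC up to 0.74) and about 4 to 6 points for strong ones. At an assumed 25% vs 10% it is about 1 to 13 points over AUC 0.50 to 0.82. All of these rest on an assumed prognostic strength. The change is worth making because it is nearly free and the gain is largest where the plan is most exposed, namely if placebo response exceeds 3%.

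**What to change.** In section 6.2, before unblinding, prespecify an analysis of the primary endpoint that:

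- adjusts for baseline log10 HBV DNA and baseline ALT (as a multiple of the cutoff), and for no longer list of covariates;
- is fitted once across the three arms, by a method suited to sparse events, such as a Firth penalised likelihood-ratio test or a covariate-adjusted score test;
- reports a standardised risk difference with 95% CI for each dose against placebo;
- states that baseline HBV DNA is the reference-laboratory value. Section 4.4.2 has screening tests done at the centres and repeated at the reference laboratory, so two values exist.

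Keep the chi-square or Fisher test alongside as the sensitivity analysis, and add the same two baseline terms to the GEE.

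The cost is protocol wording and slightly more analysis work, with no new data or patients. The downsides are a little conservatism or shrinkage when placebo events are very few, and a loss of about 1 point of power or less if the covariates turn out not to be prognostic.
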